#### 8.1.4 Study parameters tested in controls

The control group will be the group starting with complementary feeding at the corrected age of 17 weeks. All parameters will be tested in the intervention group and in the control group.

Control group B:

- Growth parameters: Length, weight and head circumference at 3 months (with an age range of 2 weeks), and 1 year and 2 years of age (with an age range of 6 weeks).
- Other parameters (see 8.1.3)
- BEBQ (questionnaire) at 10-12 weeks of age, supplemented with questions regarding the baby feeding
- Food diaries at 6 months, 9 months, 1 year and 2 years of age, supplemented with questions about the start of complementary feeding (retrospective)

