**Allergies:** Lastly, there are contrasting reports on the risk of developing food allergy due to early exposure of solid foods. It was thought that with early introduction of solid food the preterm infant might have a risk of developing food allergy. An observational study investigated 257 preterm infants born in the UK showed that infants who had 4 or more solid foods introduced at <17 weeks of corrected age had an increased risk (odds ratio (OR) 3.49; 95%CI 1.51-8.05) of developing eczema by 12 months of corrected age. This study also reported that the introduction of solid foods prior to 10 weeks of corrected age was associated with an increased risk (OR 2.94; 95%CI 1.57-5.52) of eczema development. However, information was collected retrospectively on solid food practices (recall bias). The relation between food hypersensitivity and atopic dermatitis is controversial. A Danish Allergy Research Centre Cohort, including 562 children, found that only 15% of the children with constitutional eczema also had a food allergy. More recent papers are in contradiction with the study above. Liem et al investigated whether premature or low birth weight children have an increased risk of developing food allergy compared with term or normal birth weight children from birth to seven years. They studied a birth cohort of 13,980 children, of which were 881 preterm children (6.3%), in Canada. According to this study immaturity of the gastrointestinal tract or immune response does not seem to change the risk for development risk for allergies. Kvenshagen et al found no difference in the prevalence of eczema/atopic dermatitis at 2 years of age between 32/161 (19.9%) children born preterm and 63/351 (17.9%) born at term. There was also no difference in the prevalence of IgE-mediated food allergy in children with atopic dermatitis between infants born preterm (2/32, 6.2%) and term (6/63, 9.5%). According to the most recent literature it seems that preterm infants are no more likely to develop atopic disease than term infants.

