**Measurements for control group B (term born children)**

The term born infants will be enrolled in two hospitals, or obstetric practices and well baby clinics affiliated with the hospital, in which the preterm infants are also enrolled. The parents of the term infants will be informed with a brochure by the midwife, nurse or medical doctor during a obstetric practice visit, outpatient clinic/well baby visit or during the hospital stay/visit for the delivery. If parents give approval to the midwife or doctor, the midwife or doctor will inform the researcher or research nurse. They will contact parents by phone and provide additional information and give or send the information letter and informed consent form to the parents. Parents will be give at least one week to consider their decision after receiving the information letter and informed consent form. Informed consent will be taken by the researcher or research nurse. Treatment or follow-up of the term born child will not change depending on participation in this study. Parents will be given at least one week to consider the information before making the decision on participation. If there are no further questions, informed consent will be taken.

Parents of the term born infants are asked to:

- Fill in the BEBQ and a questionnaire regarding parental characteristics (see 8.1.3) when their child is 3 months old
- Send information to the researchers about the growth parameters (length, weight, head circumference) of their child at 3 months, 1 year and 2 years old, obtained at the well baby clinic
- Fill in four food diaries when their child is 6 months, 9 months, 12 months and 24 months old

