### 8.3.10 Dietary intake – Extra in this study

Parents of all children (preterm infants and term born infants (control group B)) are asked to complete three different diaries during the study period until the age of 2 years. The diaries will be pilot tested. Possibly, the diaries will be collected via a digital website.

- Version 1 (Milk diary): A diary about the breast- or formula milk before the start of complementary feeding.
- Version 2 (Start diary): A diary at the start of complementary feeding. Parents are asked to fill in when they give solid food for the first time, what kind of solid food they give and how much their child eats for the first time.
- Version 3 (2 day diary): A 2-day diary method: Parents will be asked to fill in the food diary during two days, of which one day in the weekend. Parents are asked to do this at the age of 6 months, 9 months, 1 year and 2 years.

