For control group B, the preterm infants will be compared with the term infants to determine the difference of growth parameters, BEBQ results and food diaries before the start of complementary feeding, at 1 year and at 2 years of age. Growth parameters and BEBQ will be presented as continuous parameters (mean and sd or median with interquartile range). The growth parameters will be compared with the most recent Dutch growth curves. For the analyses, a t-test or nonparametric test will be used.

To take into account repeated measurement on the infants (non)linear mixed models will be used with infant as random factor and treatment (intervention, control), time and

time\*treatment as fixed factors. Infant and hospital will be added as random intercept. Random slopes will be added for time dependent variables.

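### Protocol sections disagree on which diaries control group B completes, so the planned preterm-term diary comparison before solids may have no term diary

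*Protocol*

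**What the plan says.** Two places are written specifically for control group B. In section 3, the list of what term parents are asked to do reads "Fill in four food diaries when their child is 6 months, 9 months, 12 months and 24 months old". Section 8.1.4 gives the same ages and adds how the start of solids is obtained: "supplemented with questions about the start of complementary feeding (retrospective". Neither mentions a diary before 6 months or one kept at the first solid food.

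Section 8.3.10 says something else: "Parents of all children (preterm infants and term born infants (control group B)) are asked to complete three different diaries". The first of the three is "A diary about the breast- or formula milk before the start of complementary feeding", the second is filled in when solid food is first given, and the third is the 2-day diary at 6, 9, 12 and 24 months.

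Section 10 then compares preterm with term infants on growth parameters, "BEBQ results and food diaries before the start of complementary feeding, at 1 year and at 2 years of age".

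**The concern.** The sections describe different data collection for the same infants. A site working from the group B lists would hand term parents neither the milk diary nor the start diary; a site working from section 8.3.10 would hand out both. A diary not kept before solids cannot be recovered later, and no analysis plan can repair that.

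Two things are at stake if the group B lists prevail. First, section 10 names a diary comparison at a time when only the preterm infants have a diary. Second, the date and content of the first solids would come from recall in one population and from a contemporaneous record in the other, so a difference between them could partly reflect how the question was asked. The protocol knows this weakness: in section 1.1.1 it qualifies an observational eczema study because "information was collected retrospectively on solid food practices (recall bias" was a problem there.

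**Working it through.** The protocol states no figure on this point to reproduce. The check sets the sections side by side.

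**1. What each section gives a term infant**

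| Source | Milk diary | Start diary | Diaries at 6, 9, 12, 24 months | Start of solids known from |
|---|---|---|---|---|
| Section 3, group B list | not listed | not listed | 4 | not stated |
| Section 8.1.4, group B | not listed | not listed | 4 | retrospective questions |
| Section 8.3.10 | 1 | 1 | 4 | start diary |

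That is 4 diaries per term infant under the group B lists and 1 + 1 + 4 = 6 under section 8.3.10.

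**2. What the preterm infants have.** The milk diary is taken at the first hospital visit (section 3). The start diary is described in sections 3 and 8.3.10, and section 5.5 says that the diaries will show when solids were begun. The preterm infants therefore have all 6 diaries on any reading.

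**3. Mapping to section 10.** It names three times: before solids, 1 year and 2 years.
- Under section 8.3.10, term infants have a diary for 3 of 3.
- Under sections 3 and 8.1.4, they have one for 2 of 3. The earliest term diary is at 6 months. The introduction cites a recommended start between 4 and 6 months in some countries, and a limit of 26 weeks. A 6-month diary would precede solids only in the late starters, a selected subset, and it is not designed as a milk diary.

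**4. Is one schedule just a shorter version of the other?** Unlikely. The retrospective questions in section 8.1.4 would be largely redundant if term parents kept the start diary.

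**5. Other early feeding data in group B.** Section 8.1.4 adds feeding questions to the BEBQ at 10-12 weeks. It also applies section 8.1.3 to group B, and that section lists the type of feeding up to solids among the items collected prospectively. Some pre-solids feeding information therefore exists on any reading, but not in a form comparable with the preterm milk diary.

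**6. A related mismatch.** Section 3 places the group B BEBQ at 3 months and section 8.1.4 at 10-12 weeks. A milk diary tied to that questionnaire needs one stated age.

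**The case against.** The strongest reply is that section 10 is loosely worded and should not be read as every measure at every time. The BEBQ is a milk-phase questionnaire taken only before solids, so the sentence cannot mean a BEBQ at 1 or 2 years. Read with the sub-objectives in section 2, it could mean BEBQ before solids, growth at all three times, and diaries at 6, 9, 12 and 24 months. No sub-objective asks for a pre-solids diary comparison with term infants. This stands as a possible reading and limits how firmly one can say that a planned comparison lacks data. It does not remove the conflict between the group B lists and section 8.3.10, and section 10 as written does include pre-solids diaries.

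A second reply is that two passages written for group B agree against one general section, so section 8.3.10 may be the error. That is fair, and it is why the fix has a second route. But section 8.3.10 names control group B explicitly, so it cannot be set aside as a sentence about preterm infants only.

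Several stronger conclusions might be inferred and are not supported:
- That the start of solids is recalled in term infants as a settled fact. This holds only if section 8.1.4 governs.
- That group B has no pre-solids feeding data. It has no diary; other items are planned.
- That sub-objective 5 depends on a preterm-term comparison. It does not mention group B, and no section specifies a preterm-term test of start age, which in preterm infants is set by allocation.
- That recall error can be scaled against the 17 − 12 = 5 weeks between the randomised arms. Both arms record the start in diaries, so term recall cannot affect that contrast, and the protocol gives no figure for recall error.

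**Conclusion.** The contradiction is in the current text and should be resolved. Its consequence is conditional: if sections 3 and 8.1.4 are followed, control group B has no diary designed for one of the three time points in section 10, and the start of solids is ascertained differently in term and preterm infants. If section 8.3.10 is followed, neither holds.

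The matter is minor. It touches only a non-randomised secondary comparison. The randomised comparison of early with late introduction, including the primary endpoint, is unaffected. The conclusion rests on taking section 10 as written, with diaries included at the pre-solids time point. No numerical size for recall error can be given from the protocol, and none is needed for the point to stand.

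**What to change.** **Preferred, if term infants can still be given the forms.** Amend the group B lists in sections 3 and 8.1.4 to agree with section 8.3.10, so that term parents complete the existing milk diary at the time of the pre-solids BEBQ and the existing start diary at the first solid food. State one age for that BEBQ in both sections. The cost is two short existing forms and slightly more burden on term parents.

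**If term infants have already been enrolled without these forms.** Section 10 opens by indicating that the target sample size was not reached, so recruitment may be over. In that case correct section 8.3.10 to exclude group B from the milk and start diaries, remove the pre-solids diary comparison with group B from section 10, and report the term start age as recalled, noting that the preterm values come from diaries. The cost is one secondary comparison.

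On either route, reword the section 10 sentence so that each measure is paired with the times at which it is taken.

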## 8.2 Randomisation, blinding and treatment allocation

Stratification will take place according to center. In order to keep the number of subjects in the different groups closely balanced at all times block randomisation will be used. According to Altman the block size used is a multiple of the number of treatments. A blocked randomization schedule (randomly permuting blocks of four and six) at a time will be used. The randomisation will be computer generated by Castor edc. Twins will be randomized as well; the first twin will be randomized into one of the two groups, the second twin will be assigned to the same group. Patients will be randomised to introduction of complementary feeding at the corrected age of 12 weeks (intervention group) and to introduction of complementary feeding at the corrected age of 17 weeks (control group) (1:1). The allocation of the timing of the start of treatment will not be blinded.

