### 4.3 Sample size calculation

The sample size calculation for this study is based on previous reported effects. In a population based study Jingxiong et al reported that introduction of complementary feeding before the age of 4 months resulted in a 76% higher odds in developing overweight than children introduced to complementary feeding after 4 months. Overweight in this study was defined as weight-for-length/height  $\geq 2$ SD above the median of the WHO reference for sex, i.e. weight-for-length/height z-score  $\geq 2$ SD. A study by Young et al reported that excess weight gain (defined as gaining  $\geq 0.5$  in weight-for-age Z-score) between 4 to 6 months was associated with an odds ratio of 2.5 for overweight at 18-24 months. This led to the conclusion that rapid early weight gain, for example due to early weaning, could result in obesity since known post-natal risk factors for obesity are rapid early weight gain and early weaning. Based on these studies we expect that the introduction of early complementary feeding in children will result in a higher prevalence of overweight children at the age of 2 year in comparison to later introduction of complementary feeding. Based on the given odds ratio of 1.76 and 2.5 an odds ratio of 2.3 was used to calculate our sample size. In 2009, the prevalence of overweight was 8% in two year old children in the Netherlands. Overweight was determined by measuring the BMI. BMI was calculated as weight/height and expressed as kg/m^2. Overweight and obesity prevalence rates were calculated using International Obesity Task Force (IOTF) cut-of values. In this study, the same calculation and definition will be used. Information of the prevalence of overweight in premature infants is lacking. Bocca-Tjeertes et al has shown that preterm infants are a growth restraint compared to term infants. On the other hand, Euser et al found a greater fat mass normalized for weight in preterm infants. Given this contrasting information on preterm infants, a slightly lower prevalence of overweight of 6% was used to calculate the sample size. Using the odds ratio of 2.3, the intervention group will have a prevalence of overweight of 13%. With a 0.05 significance level and a power of 80% a minimal sample size of 275 patients per group is required to detect a significant increase in the prevalence of overweight. Loss to follow-up is

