## 10. STATISTICAL ANALYSIS

Since the sample size was not archived, the data will be interpreted with caution. Data will be analyzed on an intention to treat basis. In addition, we will also perform a per protocol analysis, taking into account the attrition rate. In case of missing values we will use multiple imputation. For the per protocol analysis, the criteria for the start of complementary feeding will be 12-13 weeks for the early group and 16-17 weeks for the late group. A p-value of 5% will be regarded as statistically significant and results will be presented with 95% confidence intervals.

Categorical data will be presented in absolute numbers and percentages. If a metric variable is normally distributed results will be shown in mean and standard deviation (sd). If a metric variable is not normally distributed median will be used with the interquartile range.

Descriptive data on BMI will be compared with the most recent Dutch growth chart. For the primary study parameter, the prevalence of obesity, the percentage of patients that develop overweight by using the IOTF will be calculated and intervention group and control will be compared including prevalence ratios with 95% confidence intervals. Furthermore, BMI and BMI z-scores between the intervention and control group will be compared as continuous variables.

The results of the questionnaires (BEBQ, CFQ, ITQoL / PedsQL, ASQ) will be analysed according to the scoring tables attached to the questionnaires. Allergy will be scored by a SCORAD form and can be presented as continuous or categorical variable. All blood and faeces results will be analysed as continuous or categorical variable. The diary results will be analysed as a continuous variable.

For all sub-objectives (as formulated in chapter 2), the intervention group and control group will be compared to determine the effect of early versus late introduction of complementary food, using a independent t-test or nonparametric test. For subgroup analysis, i.e. for children with respiratory problems or tube feeding, logistic regression will be used.

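### Co-twins are always allocated to the same arm, but the sizing and the named between-arm analyses contain no family level, so standard errors come out modestly too small

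*Protocol*

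**What the plan says.** Protocol section 8.2 sets 1:1 allocation, stratified by center in permuted blocks, and adds a rule for twins: "the first twin will be randomized into one of the two groups, the second twin will be assigned to the same group". The second twin has no allocation of its own.

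Protocol section 4.3 sizes the trial on overweight at 2 years. For the control rate, "a slightly lower prevalence of overweight of 6% was used to calculate the sample size" percent-for-percent as written, and an odds ratio of 2.3 is taken to give 13% in the early group. Then: "With a 0.05 significance level and a power of 80% a minimal sample size of 275 patients per group is required". Allowing 5% loss gives 579 children, rounded up to 600. The section mentions no twin share, within-pair correlation or design effect.

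Protocol section 10 plans the following:
- **Primary outcome:** the arms are compared on the percentage overweight, with prevalence ratios and 95% intervals. No variance method is named.
- **Sub-objectives:** the arms are compared "using a independent t-test or nonparametric test".
- **Subgroup questions** such as respiratory problems or tube feeding: logistic regression.
- **Repeated measurements:** mixed models in which "Infant and hospital will be added as random intercept".

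No family, mother or twin-pair term appears anywhere. Section 10 also records that the planned sample size was not reached.

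**The concern.** Co-twins share parents, home and feeding environment, so their BMI can be expected to correlate positively. When both sit in the same arm, that correlation adds to the variance of the difference between arms. An analysis that treats the two infants as independent leaves the extra variance out, so its intervals are too narrow and its p-values too small.

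The hospital intercept does not repair this, because it gives co-twins no more correlation than two unrelated infants from the same hospital. The infant intercept links repeated measurements on one child, not two siblings.

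At stake are the 5% significance level that section 10 sets for itself and the power claimed in section 4.3. The point estimate is not biased by this mechanism, and allocating twins together is not a fault in itself.

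**Working it through.** **1. Reproduce the plan's figure.** Inputs from section 4.3: 6% and 13%, alpha 0.05 (taken as two-sided, since sidedness is not stated), power 80%. The mean rate is 0.095.

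n per arm = [1.96·√(2·0.095·0.905) + 0.8416·√(0.06·0.94 + 0.13·0.87)]² / 0.07² = (0.8128 + 0.3465)² / 0.0049 ≈ 274.2, so 275. Then 550 / 0.95 = 578.9, so 579.

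Both figures match exactly, and the formula is the one for independent infants. Power is 80.1% at 275 per arm. The 600 planned children leave 600 × 0.95 / 2 = 285 per arm, with 81.5% power before any clustering.

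**2. Design effect.** Let f be the share of infants in co-enrolled pairs and ρ the within-pair correlation. With both twins in one arm, the variance of an arm mean is multiplied by DE = 1 + f·ρ. Then:
- effective n = n / DE
- unadjusted standard error too small by a fraction 1 − 1/√DE
- actual two-sided alpha of an unadjusted test = 2·[1 − Φ(1.96/√DE)]

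**3. Assumptions (not in the protocol).** f = 0.2–0.4. Within-pair correlation of the underlying BMI trait = 0.3–0.7.

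**4. Convert to the binary outcome.** Overweight is a dichotomised BMI, and cutting a trait in its tail shrinks the correlation. I assume a bivariate-normal latent trait cut at 9.5% prevalence, and ρ_binary = [P(both overweight) − 0.095²] / (0.095·0.905). Latent 0.3, 0.5 and 0.7 then give 0.127, 0.245 and 0.405.

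**5. Results.**

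| Outcome | f | ρ used | DE | SE too small by | Actual alpha | Power at 275/arm | Power at 285/arm |
|---|---|---|---|---|---|---|---|
| Overweight, low end | 0.2 | 0.127 | 1 + 0.2·0.127 = 1.025 | 1.2% | 5.3% | 79.1% | 80.5% |
| Overweight, high end | 0.4 | 0.405 | 1 + 0.4·0.405 = 1.162 | 7.2% | 6.9% | 73.9% | 75.5% |
| Continuous BMI, low end | 0.2 | 0.3 | 1.06 | 2.9% | 5.7% | – | – |
| Continuous BMI, high end | 0.4 | 0.7 | 1.28 | 11.6% | 8.3% | – | – |

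The power columns use n / DE in the formula of step 1 and describe an analysis that allows for the pairs correctly. For overweight, the effective numbers are 275/1.025 ≈ 268 down to 275/1.162 ≈ 237, and 285/1.025 ≈ 278 down to 285/1.162 ≈ 245.

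**6. Break-even.** 275 per arm keeps 80% only while DE ≤ 275/274.25 = 1.003. 285 per arm keeps it while DE ≤ 285/274.25 = 1.039.

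**The case against.** **The primary method is not tied to independence.** Section 10 asks for prevalence ratios with 95% intervals and names no model or variance estimator. A cluster-robust interval would fit that wording, and a statistical analysis plan that is not shown could specify one. This stands: for the primary, the gap is an omission rather than a stated wrong method. It does not cover the independent t-tests or the listed random intercepts, which the protocol itself fixes without a family level. Nor could a later plan change how the 275 was derived.

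**A reader might infer that 80% power is flatly not delivered.** The documents do not support that. Section 4.3 rounds up to 600 children, and the 285 per arm left after 5% loss absorbs a design effect of up to about 1.04. At the low end of the assumed range, power is still 80.5%. Section 10 also already concedes that the target was missed, so actual power is short for a separate reason.

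**A reader might apply a correlation of 0.3–0.7 directly to overweight** and report alpha up to 8.3% and power down to 70%. That range describes BMI as a continuous trait. Under the latent-normal model even a latent correlation of 0.9 gives only about 0.65 for binary overweight, so those extremes do not belong to the primary outcome.

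**A reader might infer that every secondary comparison is anti-conservative.** That is too broad. The logistic regressions concern exposures such as intubation or tube feeding, which can differ between co-twins. Ignoring the pairing there can make standard errors too large rather than too small. The argument covers contrasts between the randomised arms.

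**Conclusion.** The concern holds for the between-arm comparisons. The allocation rule creates same-arm pairs, the methods that section 10 names have no family level, and the sample size assumes independent infants. The direction is certain for any positive within-pair correlation.

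The size is modest and rests on two quantities that the protocol does not give. Under the assumptions above, a nominal 5% test of overweight runs at about 5.3–6.9%, and correctly analysed power is about 74–79% at 275 per arm or 75.5–80.5% at 285. Unadjusted tests of continuous measures such as BMI z-score can run at about 5.7–8.3%. Because the target was not reached, the validity of the intervals now matters more than the planned power.

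**What to change.** **Section 10.**
- Estimate the primary prevalence ratio with a log-link (modified Poisson) model, using GEE or robust variance clustered on mother or family.
- Add a family random intercept to the mixed models, with infant nested in family.
- Replace the independent t-tests and nonparametric tests for between-arm comparisons with clustered equivalents.
- Report the number of twin pairs per arm.

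**Section 4.3.** State that 275 per group assumes independent infants, restate the power with a design effect and its assumed inputs, and note that the target was not reached.

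**Cost.** A few lines of text and code. No new data are needed, because pair membership must be known to apply the allocation rule. Intervals become slightly wider and the stated power slightly lower.
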